### Data management, processing, and dissemination

At the outset of the baseline study, each participant will be assigned a unique identifier that will remain confidential throughout the study. All collected data will be securely stored in the data management software, and access to this information will be restricted without prior authorisation. The members of IEC and CTRI will monitor all data. De-identified/coded data will be extracted from the data management system as CSV files at all three centres. This will then be transferred to Microsoft Excel and subsequently to SPSS (version 21.0; IBM Corp., Armonk, NY, USA). In compliance with the ICMR (Indian Council of Medical Research) Ethical Guidelines, the data will be stored for a minimum of 5 years. These data may be used for follow-up of participants to assess the long-term effects of the intervention.

The results will be published in open-access journals and presented at National & International conferences. All findings from the trial will be notified to the IEC and CTRI.

### Statistical analyses

Primary outcome measures will be analysed using two-sided statistical tests with a type I error rate of α = 0.05. Primary analysis will be performed using the intention-to-treat method. Categorical data will be compared between the two groups using chi-square or Fisher’s exact tests. Continuous data will be evaluated using parametric or non-parametric tests based on data distribution.

For outliers (± 3 standard deviation), efforts will be made to cross-check and obtain the correct values. Failing this, the case will be considered as missing data. In the case of random missing values, two separate analyses will be performed: one including the cases with missing data by choosing pairwise deletion and the other excluding it using listwise or case-wise deletion. A complete case analysis will be considered if differences are observed between the two analyses. In the case of non-random missing values, the imputation method may be used by replacing the missing value with the mean for that variable.

Potential adjustments for baseline values, age, gender, and disease duration may be considered. Multivariable linear and logistic regression analyses will be used to determine predictors of remission. Finally, subgroup analyses may be performed based on factors such as gender, age, comorbidity, diagnosis length, and severity to investigate potential variations in treatment responses.

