**Methods:**

The DiRemI study is a prospective, open-label, matched-group trial aimed at assessing the impact of a one-year online integrated intensive lifestyle intervention (ILI) comprising dietary modifications, physical activity, psychological support, and medical management on weight loss and remission in adult T2D patients (aged 30–70 years), with a body mass index (BMI) between 25 and 35 kg/m^2^, and disease duration of <15 years. ILI will be compared with routine medical care (RMC). Participants will be recruited from three clinics: one providing ILI and two others providing RMC. The co-primary outcome will be weight loss and remission at 12 months, with a follow-up at 18 months. The proposed sample size is 360 participants (180 each in intervention and control group).

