### Specific objectives (as specified during ethics submission)

The primary objective of the intervention is to achieve a weight reduction of ≥ 10% and an HbA1c level of <6.5% without pharmacotherapy, with the ultimate goal of achieving diabetes remission. The secondary objective of the intervention is to evaluate its effect on other aspects of diabetes outcomes, including mental health (anxiety and depression), comorbidities (hypertension and dyslipidaemia), diabetes-related complications (nephropathy), and biochemical parameters (serum lipids, liver function tests, and kidney function tests).

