### Sample size determination

We calculated the sample size for our study using Bonferroni correction to adjust for two primary outcome measures: weight and HbA1c. With an overall alpha level of 0.05, the adjusted significance level for each outcome was set to 0.025. Assuming a power of 95%, the required sample sizes were determined based on Cohen’s d effect sizes of 0.445 for weight and 0.635 for HbA1c, based on a previous study by Lean et al. (2018) [18]. The calculations indicated a sample size of 132 participants per group for weight and 65 participants per group for HbA1c level. To ensure adequate power for both outcomes, we selected the larger sample size requirement, resulting in a total sample size of 132 participants per group. To account for the potential dropout and loss to follow-up of 30%, the final sample size was estimated at 360 (180 in each group).

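### The stated per-outcome level of 0.025 matches neither the two-sided 0.05 in the analysis section nor the sample size figures, and no rule says whether one or both primary outcomes must succeed

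*Protocol article*

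**What the plan says.** Three places in the protocol article bear on the level of the primary tests.

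- *Sample size determination* says the size was calculated "using Bonferroni correction to adjust for two primary outcome measures: weight and HbA1c", and continues: "With an overall alpha level of 0.05, the adjusted significance level for each outcome was set to 0.025". It assumes 95% power and "effect sizes of 0.445 for weight and 0.635 for HbA1c", and arrives at 132 per group for weight and 65 for HbA1c. It takes the larger figure and sets 180 per group to allow for 30% dropout. It does not say whether its tests are one- or two-sided.
- *Statistical analyses* says: "Primary outcome measures will be analysed using two-sided statistical tests with a type I error rate of α = 0.05". It mentions neither 0.025 nor Bonferroni nor any other multiplicity rule, and does not say whether 0.05 applies to each outcome or overall.
- The abstract's *Methods* paragraph says: "The co-primary outcome will be weight loss and remission at 12 months, with a follow-up at 18 months". *Outcome measures* lists the two as separate items, (a) and (b). Neither place says what counts as success for the trial.

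**The concern.** A Bonferroni split has a purpose only if success on either outcome would support a claim. The word co-primary is commonly used where both outcomes must succeed, and then each can be tested at the full level. The document uses the first device in the sizing section, the second word in the abstract, and a plain 0.05 in the analysis section.

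A result of p = 0.03 on one outcome shows the consequence. It fails at the level in the sizing section and succeeds at the level in the analysis section, if that level applies to each outcome. Unless the rule is settled before analysis, it could be chosen with the results in view. The study is open-label and not randomised, so it has little room for a flexible success criterion.

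The stated 95% power is affected too, because it depends on the level actually used in the calculation.

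**Working it through.** **Inputs.** From *Sample size determination*: d = 0.445 (weight), d = 0.635 (HbA1c), power 95%, equal groups, 132 and 65 per group, 180 per group after allowing for 30% dropout. From *Statistical analyses*: two-sided tests, 0.05. The correlation between the two test statistics is not given, so a range is used.

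**1. Reproducing the plan's figures.** The normal formula per group is n = 2(z_level + z_power)² / d², with z_power = 1.645.

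- Two-sided 0.05 (z = 1.960): (1.960 + 1.645)² = 12.99. Weight: 2 × 12.99 / 0.1980 = 131.2, so 132. HbA1c: 2 × 12.99 / 0.4032 = 64.5, so 65. Both stated figures are reproduced.
- Two-sided 0.025 (z = 2.241): (2.241 + 1.645)² = 15.10. Weight: 2 × 15.10 / 0.1980 = 152.5, so 153. HbA1c: 2 × 15.10 / 0.4032 = 74.9, so 75. Neither stated figure is reproduced.

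A noncentral t calculation gives 132.2 and 65.4 at two-sided 0.05, and 153.8 and 76.2 (154 and 77 rounded up) at two-sided 0.025. One-sided 0.025 is numerically the same as two-sided 0.05 and also gives 132 and 65, but the analysis section specifies two-sided tests. One-sided 0.05 gives 110 and 54.

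**2. Family-wise error if each outcome is tested at the stated level and either success counts.** Under independence this is 1 − (1 − level)². At 0.05: 1 − 0.95² = 9.75%. At 0.025: 1 − 0.975² = 4.94%. With correlated normal statistics it is 1 − P(|Z1| < c, |Z2| < c):

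| Correlation | Each at 0.05 | Each at 0.025 |
|---|---|---|
| 0 | 9.75% | 4.9% |
| 0.3 | 9.5% | 4.8% |
| 0.5 | 9.1% | 4.6% |
| 0.7 | 8.3% | 4.3% |
| 0.9 | 7.0% | 3.6% |

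If both outcomes must succeed, the chance of a false overall claim is at most 5% with each at 0.05.

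**3. Power.** The normal approximation is power = Φ(d√(n/2) − z_level). After 30% dropout, 180 × 0.7 = 126 remain per group.

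| n per group | Outcome | Two-sided 0.05 | Two-sided 0.025 |
|---|---|---|---|
| 132 | weight | 95.1% | 91.5% |
| 126 | weight | 94.2% | 90.2% |
| 132 | HbA1c | 99.9% | 99.8% |
| 126 | HbA1c | 99.9% | 99.7% |

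For example, weight with 132 at 0.025: 0.445 × √66 = 3.615; 3.615 − 2.241 = 1.374; Φ = 91.5%.

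**4. What each decision rule does to power.**

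- *Holm.* Weight can be claimed at 0.05 once HbA1c has passed 0.025. The power for weight is therefore at least 95.1% + 99.8% − 100% = 94.9% with 132, and 94.2% + 99.7% − 100% = 93.9% with 126, provided the planned HbA1c effect is real.
- *Both must succeed, each at 0.05.* Joint power is at least 95.1% + 99.9% − 100% = 95.0% with 132, and 94.2% + 99.9% − 100% = 94.1% with 126.

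**The case against.** The strongest reply is that the two sections can be reconciled. The analysis section speaks of the primary outcome measures in the plural and does not say that 0.05 applies to each. The sizing section calls 0.05 the overall level and 0.025 the level per outcome. On that reading the analysis section repeats the overall level, and the split is already prespecified. This reading is possible, so a 9.75% error rate cannot be called an established property of the plan. But nothing in the analysis section says so, and the reading leaves the sample size figures unexplained: for two-sided tests they do not contain the split.

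A reader might also infer that the trial really was sized at 0.025 per outcome and that only the analysis section is at fault. The text says 0.025, but the arithmetic does not support it. Correcting the analysis section alone would leave the stated power for weight wrong.

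A reader might take *Specific objectives* as a third, conflicting decision rule, since it says the intervention is to "achieve a weight reduction of" at least 10% and also bring HbA1c below 6.5% without drugs. That sentence describes a treatment goal and does not set a rule for testing hypotheses, so it should not be counted as evidence either way.

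Finally, the practical effect is limited. At the planned weight effect, the chance that p falls between 0.025 and 0.05 is only 95.1% − 91.5% = 3.6% with 132 per group, or 94.2% − 90.2% = 4.0% with 126. This shows the conflict is unlikely to decide the trial if the planned effect is true. It says nothing about the error rate when there is no effect. Procedural detail may be left to an analysis plan, but here two levels are stated and they differ.

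**Conclusion.** The point stands as an inconsistency in the stated rule and the stated power. The per-outcome level of 0.025 in the sizing section conflicts on its face with the two-sided 0.05 in the analysis section, and the figures 132 and 65 agree with the latter.

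The size of the error inflation is conditional. It reaches 9.75% only if 0.05 applies to each outcome, either success counts, and the two statistics are independent. Weight loss and remission are plausibly positively correlated, which would put it lower: about 9.1%, 8.3% or 7.0% at correlations of 0.5, 0.7 or 0.9. If both must succeed, there is no inflation. The document does not support a claim that the plan's error rate simply is 9.75%.

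The power figures rest on the plan's own continuous effect sizes and the normal approximation. They describe the sizing as written, not the power of tests on the two responder-type outcomes listed under *Outcome measures*, which is a separate matter.

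**What to change.** State the decision rule in *Statistical analyses* and make *Sample size determination* agree with it. This should be done before any outcome data are analysed.

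- **If either outcome suffices:** test the two by Holm at family-wise two-sided 0.05, the smaller p-value against 0.025 and, if that succeeds, the other against 0.05. Plain Bonferroni at 0.025 each is also valid; Holm is never less powerful. In the sizing section, say that 132 per group gives about 91% power for weight at the 0.025 level, or about 90% with the 126 left from 180 after 30% dropout, not 95%.
- **If both must succeed:** say so, test each at two-sided 0.05, and delete the Bonferroni text. The figures 132 and 65 then agree with 95% power per outcome.

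The cost is a sentence or two in each section and, under the either-outcome rule, a slightly lower stated power. No added patients are needed. Holding 95% power for weight at the 0.025 level itself would take 153 / 0.7 = 219 per group (220 starting from 154); restating the power avoids this.

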### Setting and eligibility criteria

The proposed study will be conducted at the Freedom from Diabetes Clinic, which operates on an online subscription-based model of 1-year duration for the management of diabetes (intervention group). Additionally, the study will include participants from two private clinics in Pune and Ahmedabad (India) (Control Group), which provide standard medical care based on established guidelines for individuals with diabetes. All individuals with T2D who enrol in these centres between March and August 2024 and meet the eligibility criteria will be recruited for this study Table 1.

**Table 1 pone.0306394.t001:** Eligibility criteria for the DiRemI study.

Inclusion Criteria	Exclusion Criteria
Age between 30 and 70 years	Pancreatitis or drug-induced diabetes (Steroids)
Confirmed diagnosis of type 2 diabetes, which may be managed with oral hypoglycemic agents, insulin, Ayurvedic antidiabetic medications, or have an HbA1c level of ≥ 48 mmol/mol (6.5%) with or without medication	Other types of diabetes (type 1 diabetes mellitus, diabetes insipidus, maturity-onset diabetes of the young, latent autoimmune diabetes in adults, or Gestational Diabetes)
Body mass index (BMI) between 25 kg/m^2^ and 35 kg/m^2^	Advanced complications related to nephropathy (eGFR<30 mL/min/1.73 m^2^, urine microalbumin >1000 mg), retinopathy (severe non-proliferative diabetic retinopathy and proliferative diabetic retinopathy), neuropathy (peripheral artery disease or diabetic neuropathy resulting in complete numbness and loss of sensation, amputations, ulcers, foot deformities, Charcot’s foot)
Duration of type 2 diabetes less than 15 years	History of heart attack, cardiac arrhythmia, bypass or stent placement surgery, ischemic heart disease, angina (class II or III), myocardial infarction within the previous 6 months, reported ejection fraction <40%, abnormal ECG, and positive stress test results (moderate or severe)
Ready to provide written informed consent	Known history of cancer
Agree to undergo the examination, lifestyle intervention program, and post-program evaluation	Pregnant and lactating women
Well-oriented in time, space, and as a person	Patients who have required hospitalization for any diabetes-related complications in the last 6 months or for depression or are on antipsychotic drugs

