### Sampling and recruitment process

All patients participating in the program (intervention group) or attending the two clinics (control group) will be screened for eligibility criteria. A list of all eligible participants from each of the three clinics will be compiled every month. Participants will be selected for the study based on computer-generated random numbers until the desired sample size is achieved.

Prior to participation, all participants will be required to provide written informed consent. The consent form will outline the purpose, procedures, benefits, risks, participation requirements, contact information for the Principal Investigator, and information regarding withdrawal from the study. Consent will be collected by a trained member of the research team and stored electronically. Data will be collected at four time points: at the start of the study, at six months, 12, and 18 months after the commencement of the study.

The study period, including the schedule of enrolment, intervention, and assessment of the study groups, is shown in Fig 1.

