### Outcome measures

The primary outcome measures are a) Weight loss of more than or equal to 10% and b) Remission of T2D (HbA1c less than 6.5% for at least 3 months without medication). Secondary outcomes include a) reduction in dosage and/ or frequency/ class of drug or complete stoppage of diabetes medication, b) improved glycemic control (HbA1c less than 7% with or without medication), c) reduction in fasting glucose levels (below 126 mg/dl) and PP blood glucose levels (below 200 mg/dl) with or without glucose-lowering medications), d) improvement in diabetes-related complications (nephropathy- improvement in terms of eGFR>90 mL/min/1.73m^2^), e) improvement in comorbidities (hypertension- blood pressure ≤140/90 and dyslipidaemia- Total cholesterol <200 mg/dl, triglycerides <150 mg/dl, and HDL >40 mg/dl for males and >50 mg/dl for females), and f) improvement in mental health outcomes (anxiety and depression- Reduction in the score—below 10).

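### Arm is nested in clinic (one programme clinic, two control clinics), so the patient-level primary tests hold their 5% level for programme versus routine care only if between-clinic variation is zero

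*Protocol article*

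**What the plan says.** The Abstract (Methods) sets the layout: "Participants will be recruited from three clinics: one providing ILI and two others providing RMC". Setting and eligibility criteria places the controls in two private clinics in different cities, Pune and Ahmedabad. Under Sampling and recruitment process, "A list of all eligible participants from each of the three clinics will be compiled every month", and random numbers then choose which listed patients enter. They do not choose the arm, which follows from the clinic a patient attends.

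Both primary outcomes are binary. Outcome measures states: "The primary outcome measures are a) Weight loss of more than or equal to 10% and b) Remission of T2D". Statistical analyses states: "Primary outcome measures will be analysed using two-sided statistical tests with a type I error rate of α = 0.05". For the comparison itself it states: "Categorical data will be compared between the two groups using chi-square or Fisher’s exact tests". The adjustments it says may be considered are baseline values, age, gender and disease duration; clinic is not among them. Sample size determination has no term for clinic. The limitations in the Discussion concede that the study is not randomised and rely on a matched control group, but do not mention the one-against-two clinic structure.

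**The concern.** A chi-square or Fisher test takes its null distribution from independent patients who share one success probability. Here every patient in the programme arm shares a clinic, and every control shares one of two. Any ordinary difference in outcome between clinics therefore enters the difference between arms but not the variance against which it is judged. More patients at the same three clinics do not help, because the clinic part of the variance does not shrink with patient numbers.

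This is separate from imbalance in patient characteristics. It would remain if the patients at the three clinics were perfectly comparable, so matching or adjustment on patient-level covariates does not remove it.

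At stake is what a significant result can be said to show. The Introduction aims at the efficacy of the programme compared with standard medical care. The tests named answer a narrower question: whether the patients of the programme clinic did differently from the pooled patients of these two control clinics.

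**Working it through.** **Inputs from the protocol.** Three clinics, one against two (Abstract; Setting and eligibility criteria). 180 per group, 30% loss, d = 0.445 for weight and 0.635 for HbA1c, 95% power (Sample size determination). Two-sided 0.05 (Statistical analyses). Evaluable number after loss: 180 × 0.7 = 126 per group.

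**Assumptions, not in the protocol.** ICC between clinics of 0.005 to 0.05; control group split equally (90 + 90, or 63 + 63 after loss); clinics regarded as a sample of possible clinics.

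**1. The plan's own figure.** n = 2 × (1.96 + 1.645)² / d². For weight, 2 × 12.995 / 0.198 = 131.2, so 132. For HbA1c, 25.99 / 0.4032 = 64.5, so 65. Both reproduce, and both assume independent patients, that is, a design effect of 1. (The multiplier 1.96 corresponds to two-sided 0.05. Whether that fits the Bonferroni level stated in the same section is a separate point.)

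**2. Design effect with all clinic effects as noise.** With n per group, the variance of the difference relative to the naive variance is

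DE = {[1 + (n − 1)·ICC] + [1 + (n/2 − 1)·ICC]} / 2.

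At n = 180 and ICC 0.01: (2.79 + 1.89)/2 = 2.34. Actual rejection of a nominal 5% test is 2 × [1 − Φ(1.96/√DE)]; here 1.96/√2.34 = 1.281, which gives 20%.

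**3. Design effect with only control-clinic variation as noise.** If the single provider's own effect counts as part of the programme, the first bracket becomes 1. At n = 180 and ICC 0.01: (1 + 1.89)/2 = 1.445, which gives 10.3%.

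| ICC | n = 180, all clinics: DE, rejection | n = 180, controls only | n = 126, all clinics: DE, rejection | n = 126, controls only |
|---|---|---|---|---|
| 0 | 1, 5% | 5% | 1, 5% | 5% |
| 0.005 | 1.67, 12.9% | 7.6% | 1.47, 10.6% | 6.8% |
| 0.01 | 2.34, 20.0% | 10.3% | 1.94, 15.9% | 8.7% |
| 0.02 | 3.68, 30.7% | 15.4% | 2.87, 24.7% | 12.4% |
| 0.05 | 7.70, 48.0% | 27.5% | 5.68, 41.1% | 22.0% |

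**4. Check on the binary test.** A beta-binomial simulation of the uncorrected chi-square test (100,000 runs, 180 against 90 + 90, null rate 10%) rejects in 5.0%, 12.8%, 19.9%, 30.9% and 48.6% of runs at ICC 0, 0.005, 0.01, 0.02 and 0.05. Null rates of 5%, 20% and 30% give similar figures. Fisher's exact test is conservative, so it gives less: at 126 per group and a 5% rate, about 6%, 10%, 17% and 29–30% at ICC 0.005 to 0.05; at a 2% rate and ICC 0.01, about 5%.

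**5. Scale of the ICC.** At a 10% event rate, ICC 0.01 is a clinic standard deviation of √(0.01 × 0.10 × 0.90) = 0.03, or 3 percentage points.

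**6. Tipping ICC for binary results (126 against 63 + 63, all clinic effects as noise).** Solve

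[p₁q₁(1 + 125·ICC) + p₂q₂(1 + 62·ICC)]/126 = [(p₁ − p₂)/1.96]², where q = 1 − p.

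For illustrative results of 20%, 30% and 40% against 5%, significance is lost at ICC 0.023, 0.061 and 0.113. These values treat the ICC as known.

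**7. Why analysis cannot settle it.** A clinic-level test has 3 − 2 = 1 degree of freedom, with critical t = 12.7 at two-sided 5%. Nor can the two control clinics supply a usable estimate of clinic variation. At a 10% rate with 63 each, the sampling standard error of their difference is √(2 × 0.09/63) = 5.3 points, larger than the true clinic-difference SD at ICC 0.01, √2 × 3 = 4.2 points.

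**The case against.** The strongest reply is that the error rate depends on the question. If the three clinics are taken as fixed and the claim is confined to them, the patient-level test needs no clinic variance. That stands, so a reader should not infer that the 5% level fails outright: the documents give no ICC, and the inflation is conditional on one above zero and on the wider claim.

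A second reply is that the programme is a package from one provider, delivered online, with its own physicians and support team. Prescribing and staffing on that side are arguably treatment and not noise. This is a fair choice of estimand. It roughly halves the excess over 5% or better, but does not remove it, because the two control clinics still stand in for routine care in general.

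Third, Fisher's test with rare events can bring rejection close to 5%. True, but the protocol leaves the choice between the two tests open and gives no event rate for routine care.

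Fourth, the limitations already admit non-randomisation, and details may sit in an analysis plan that is not shown. The first does not cover clinic nesting. On the second, centre-specific contrasts could well appear there, and their absence from the article is not the fault; the point rests on the tests, level and clinic layout that the article itself fixes.

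**Conclusion.** The point holds in conditional form. For a conclusion about the programme against routine medical care, the named tests keep their two-sided 5% level only if between-clinic variation is zero. The figures tabulated above show the size under either view of the programme clinic's own effect. They rest on an assumed ICC range, an equal control split (the protocol fixes none) and a chi-square or normal test.

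Two stronger readings are not supported. One is that a significant result would necessarily be spurious: the tipping values show that very large differences would largely survive. The other is that the difference between the two control clinics could serve as a yardstick or decision rule: it is too imprecise for that, and no ICC threshold has any basis in the documents. The limit comes from the three-clinic design. Analysis can expose it but not remove it.

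**What to change.** In Statistical analyses, keep the pooled comparison and add for each co-primary outcome:

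1. The programme clinic against each control clinic separately and, descriptively only, the difference between the two control clinics.
2. The pooled result recomputed with a clinic design effect over a stated range of assumed ICCs (for example 0.005 to 0.05), together with the tipping ICC for the binary outcome. Label this a sensitivity analysis, not a pass/fail rule, and say whether the programme clinic's own effect is counted as treatment or as noise.
3. A statement, carried into the limitations and conclusions, that the result compares these three clinics and that the programme effect cannot be separated from clinic effects.

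The cost is a few lines of text and a few extra analyses. No new patients or visits are needed, since the data management section already has data extracted at all three centres. The downside is wider sensitivity intervals and a narrower claim if the effect is modest.

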#### Anthropometric and socio-demographic

During baseline assessment, participants will be requested to provide self-reported data on sociodemographic variables, including age, gender, education, and marital status, as well as anthropometric measurements such as height and weight. Detailed instructions on the precautions to be taken while measuring weight will be provided to ensure the accuracy of the self-reported data (S1 Appendix). The data will be reported as the average of three readings. Body mass index (BMI) will be calculated.

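### Values beyond 3 SD that cannot be verified are set to missing with no plausibility test, so genuine outcomes can be discarded; the likely effect is small and its direction open

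*Protocol article*

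**What the plan says.** All rules below are in the protocol article, mostly under Statistical analyses.

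- Screening: "For outliers (± 3 standard deviation), efforts will be made to cross-check and obtain the correct values".
- Default when the check fails: "Failing this, the case will be considered as missing data".
- What then happens to a missing value: if it is judged random, two analyses are run, "one including the cases with missing data by choosing pairwise deletion and the other excluding it using listwise or case-wise deletion". If it is judged non-random, "the imputation method may be used by replacing the missing value with the mean for that variable".
- Analysis principle: "Primary analysis will be performed using the intention-to-treat method".

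Other sections bear on the point:

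- Outcome measures makes a weight loss of at least 10% one of the two primary outcomes.
- Anthropometric and socio-demographic says that at baseline "participants will be requested to provide self-reported data on sociodemographic variables", and the same sentence includes height and weight. Measuring instructions are given and three readings are averaged.
- The limitations paragraph of the Discussion accepts that self-reported anthropometry may contain errors, and mentions monitoring of incoming data.
- Mode of delivery has intervention participants log weight regularly in the app. The control group section describes no such record.

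**The concern.** Distance from the mean does not show that a value is wrong. Under this rule a value need not be impossible, or shown to be mistaken, to be dropped; it is enough that it is extreme and that nobody could confirm it. A co-primary outcome asks who lost an unusually large share of body weight. If the 3 SD limit is applied to weight change, the values flagged on the loss side are large losses, so data are selected on the outcome.

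Three features add to this:

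1. Discarding observed outcomes because of their size conflicts with an intention-to-treat analysis.
2. Weight is self-reported, whereas HbA1c comes from accredited-laboratory reports. The deletion default therefore bears more on the co-primary outcome with the weaker source.
3. A log of serial weights is described for one arm only. The same extreme value could be kept in one arm and deleted in the other, in an open-label comparison that is not randomised.

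A deleted value that is judged non-random may also be replaced by the variable's mean. Where that mean lies below a 10% loss, a true responder would be recorded as a non-responder.

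**Working it through.** The protocol gives no figure on this point to reproduce, and no SD or distribution for weight change. Only the 180 per group (Sample size determination), the 10% threshold and the 3 SD limit come from the document. The rest is assumed.

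**How many genuine values are flagged?** For a normal variable, 2 × P(Z > 3) = 0.0027. That is 0.0027 × 180 = 0.49 per arm and 0.0027 × 360 = 0.97 overall, per variable. Right skew raises this: for log-normal variables with log-SD 0.3 to 1.0, 1.0% to 1.9% of valid values lie beyond 3 SD.

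**Where does the cut fall if the limit applies to weight change?** Assume a mean loss of 8% (SD 6) under the intervention and 2% (SD 4) under control.

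- Pooled limit: mean (8 + 2)/2 = 5; variance (36 + 16)/2 + 3² = 35; SD 5.92; upper cut 5 + 3 × 5.92 = 22.7% loss. Under normality the intervention tail is P(Z > (22.7 − 8)/6) = P(Z > 2.46) ≈ 0.007, or about 1.3 of 180. Almost no controls are reached.
- Within-arm limit: the upper cut is 8 + 18 = 26% loss in the intervention arm and 2 + 12 = 14% in the control arm. Control responders can now be removed, from a small base.

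**Effect on the difference in 10%-responder rate** (simulation, 4,000 runs, 180 per arm, skew 0, 1 and 1.5; removed values left out of the denominator):

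| Limit on change | Verifiable | All values kept (points) | Rule applied (points) | Shift |
|---|---|---|---|---|
| Pooled | none | 34.7 / 27.2 / 24.1 | 34.2 / 25.7 / 22.2 | -0.4 / -1.5 / -1.9 |
| Pooled | half of intervention, no control | 34.7 / 27.3 / 24.1 | 34.5 / 26.5 / 23.2 | -0.2 / -0.7 / -0.9 |
| Within arm | none | 34.6 / 27.3 / 24.3 | 34.7 / 27.6 / 24.6 | +0.1 / +0.3 / +0.4 |
| Within arm | half of intervention, no control | 34.7 / 27.2 / 24.1 | 34.8 / 27.8 / 25.0 | +0.1 / +0.6 / +0.9 |

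Shifts are taken from unrounded rates. Hand check of the two extremes, both at skew 1.5:

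- Pooled, nothing verified: the intervention rate goes from 28.9% (52.0 of 180) to (52.0 − 5.0)/(180 − 5.0) = 26.9%, and the control rate from 4.7% to 4.6%. The net shift is about -1.9.
- Within arm, unequal verification: the intervention rate goes from 28.9% to (52.0 − 1.3)/(180 − 1.3) = 28.4%, and the control rate from 4.8% (8.6 of 180) to (8.6 − 2.6)/(180 − 2.6) = 3.4%. The net shift is about +0.9.

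With the pooled limit and nothing verified, the mean difference goes from 6.0 to 5.9, 5.6 or 5.5 percentage points of weight.

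**If the limit applies to raw weight.** Assume a mean of 78 kg, SD 12, skew 1. A 10% loss is 7.8 kg, or 7.8/12 = 0.65 SD, so losing weight hardly moves a person towards a 3 SD limit. About 0.35 of 180 intervention participants are flagged. Of the 7.7 with a loss above 20%, about 0.07 are flagged.

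**The case against.** The strongest reply is that the rule requires a cross-check before anything is dropped, and that the screening scale, plausibility limits and sensitivity runs commonly belong in an analysis or data-management plan that is not shown. This stands in part. The missing scale and reference group would not be a finding alone; they matter here because they decide what the rule does. The default to missing is different: it is a stated instruction, and anyone following it would delete a credible value.

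Three stronger readings are tempting, and the document does not support them.

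- A reader might infer that self-reported weight often has nothing to be checked against. The protocol does not say so. It describes repeated readings, monitoring of incoming data, app logs for the intervention arm, and controls who attend clinics that could be contacted. What can be said is that ability to verify may differ by arm.
- A reader might infer that the rule exaggerates the treatment effect by removing control responders. A case can be built: with 97% of controls at N(−1, 3) and 3% at N(−13, 2), the within-arm cut is −12.2%, and the control 10%-loss rate falls from 2.9% to about 1% if nothing is verified. If the limit is instead pooled with an intervention arm at −8% (SD 6), the cut is −22.6%. The control rate then stays at 2.9%, the intervention rate falls from 36.9% to 36.5%, and the difference shrinks slightly.
- A reader might infer that every deleted value is then mean-imputed. That route is optional, and applies only to values judged non-random.

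The same rule could trim skewed laboratory markers, but this is a weaker point: those values come from laboratory reports, so true highs should normally be confirmed, and the section already allows non-parametric tests.

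**Conclusion.** The point holds in a limited form. As written, the rule can discard genuine observed outcomes because they are extreme and unconfirmed, and that is hard to reconcile with the stated intention-to-treat analysis. It reaches large weight losses only if the limit is applied to weight change, which the text leaves open.

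Under the assumed means, SDs and skews, about 0 to 5 intervention participants are affected and the responder difference moves by about -1.9 to +0.9 points, against a difference of roughly 24 to 35 points. The sign depends on whether the limit is pooled or within arm, and the size also depends on how verification differs between arms. A raw-weight limit changes almost nothing. The rule is therefore unlikely to decide the trial's result, and no direction of bias can be claimed. It is still worth correcting, because it lets an unspecified data-handling choice act on a co-primary outcome.

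**What to change.** Replace the default to missing under Statistical analyses with wording to this effect:

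- A value beyond 3 SD triggers a query and nothing more. State the scale (raw value or change) and the reference group (pooled or by arm).
- An unverified value that is physiologically plausible stays in the primary analysis.
- A value is set to missing only if it is confirmed wrong, or lies outside plausibility limits that are fixed before data extraction and applied without sight of group.
- A sensitivity analysis excludes the unverified extremes and reports their number by arm.

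This takes a few sentences and one extra analysis run, and needs no new data. The downside is that a few wrong but plausible values may stay in the primary analysis; the sensitivity analysis shows whether they matter.
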